**Fig. 1 Fig1:**
[figure not shown]
Schedule of enrolment, interventions, and assessments

A second questionnaire on transcultural competencies is included, which was specifically developed for the German psychotherapeutic setting, the OnTracc-questionnaire [45]. It contains 28-self-report statements, which are based on three factors, *engagement* (7 items, e.g., “I am actively involved in the process of reducing barriers for refugees and people with a migration background in accessing psychotherapy (e.g. against the shortage of translators).”), *awareness* (10 items, e.g., “I take cultural related differences in symptom description into account.”), and *challenges* (11 items, e.g., “I worry about my skills to work with refugees, because they have a different understanding of diseases and mind.”). The items are rated on a 5-point Likert scale from 1 (totally disagree) to 5 (totally agree). The OnTracc-questionnaire showed substantial convergent and discriminant validity to the MCI subscales and good reliability for all subscales (McDonald’s omega between .73 and .81) [45]. The OnTracc-questionnaire was likewise recommended for evaluating transcultural competence in training [45].

#### Secondary outcome measures

In addition to transcultural competence, secondary outcomes serve to explore concrete experiences in treating patients with diverse cultural backgrounds. Eight items are used for this purpose. For example, the number of patients with diverse cultural backgrounds who are currently being treated by each participant in their clinical practice is recorded. The participants are further asked whether they are supervised in the field of transcultural therapy and whether they have ever worked with a language mediator. A 6-point Likert scale will additionally be used to assess satisfaction in therapies with patients with diverse cultural backgrounds and perceived competence. The items were taken from a preliminary study [62].

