After each module, participants receive written feedback from a supervisor about the completed exercises and upcoming questions. The supervisors are at least bachelor-level clinical psychologists and receive regular supervision from an experienced clinical psychologist. The feedback is composed of prefabricated text templates and individualized to the participants’ responses. In the feedback, participants are complimented on their engagement; then, they receive individual feedback on the exercises they have completed. If they have noted specific questions in the module, these are also answered by the supervisor. The supervisor further encourages participants to keep up their active participation. Through sending the feedback, the next module will be unlocked. Participants are accompanied throughout the training and have the opportunity to contact the supervisors.

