#### Strategies to improve adherence to interventions {11c}

Participants are encouraged to attend the training on a weekly basis. At the end of each module, the program suggests participants to plan a timeframe to complete the next module within a week. An online calendar supports this intention. Adherence is further supported by the feedback of a supervisor, who communicates with the participants at least once a week.

If the module has not been worked on after 5 days, the supervisor sends a reminder to encourage the participant to continue. The participant is also asked if and how the supervisor can support them to continue the training. If the participant still has not continued the training 1 week later, an additional reminder email follows. If neither the training is worked on nor are the emails answered for 3 weeks, the participant receives a last e-mail where he or she is asked whether there is still interest in participation. The e-mail also contains the information that the participation will be deleted if neither there is a reply to the e-mail nor the module is processed within the next 7 days. The participant is then considered to have dropped out of the study.

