### Participant timeline {13}

Via a link, participants can access the detailed description and the inclusion criteria of the study online. After accepting the informed consent, the participants will be forwarded to the pre-training assessment (t0). During the pre-training assessment, the control variables as well as the primary (Multicultural Counseling Inventory and OnTracc) and secondary outcomes are measured. The participants will subsequently be randomized. The TG will directly start with the training. After the training (t1) and 2 (t4) and 6 months later (t5), the assessments are carried out again. The WG will complete a control assessment (t1) after the training group has completed the training. They will also complete the 2-month follow-up assessment (t2). After the 2-month follow-up assessment, they will start the training. After the training (t3) and 2 (t4) and 6 months (t5) later, they will complete the assessments. For the participant timeline, please refer to Fig. 1.

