## Data collection and management

### Plans for assessment and collection of outcomes {18a}

All data will be collected online on the Unipark survey platform via participant self-report (https://www.unipark.com). The primary (transcultural competence) and secondary outcomes (experiences in treating patients with diverse cultural backgrounds) will be collected at each time point of measurement (pre, post, follow-up 1, follow-up 2). Control variables (sociodemographic information and therapeutic practice) will be assessed at baseline only. After training, satisfaction with the training (e.g., scope, practicability, formal design) will be assessed. For an overview of which questionnaires are applied at which time point, please refer to Fig. 1. For detailed information regarding the questionnaires, see {12}.

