## Oversight and monitoring

### Composition of the coordinating center and trial steering committee {5d}

The trial team consists of six researchers who exchange information on the progress of the study at two-week intervals. The principal investigator holds ultimate oversight of the study. The study coordinator is responsible for data collection and mentoring the supervisors. The supervisors are in charge of supervising the participants, i.e., they give feedback on the modules completed. The supervisors and the study coordinator will meet on a weekly basis to discuss upcoming issues concerning the supervision of participants. Due to the small project team, a Trial Steering Committee will not be constituted.

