Finally, in a training of transcultural competence, the aspect of awareness, self-awareness, and self-reflection is essential [31]. This aspect is facilitated in exchange with other participants, which the online training does not allow. Nevertheless, we intended to create a sense of companionship with the three fictional therapists who also “attend” the training. These therapists repeatedly complement exercises with their own responses and self-reflections. Furthermore, the exchange with the accompanying supervisor remains possible at any time.

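### As described, the secondary item on supervision in transcultural therapy does not separate outside supervision from contact with the study's own supervisors, so this one exploratory comparison may lean towards the training

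*Protocol article*

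**What the plan says.** The protocol article (Outcomes {12}, Secondary outcome measures) lists eight items on concrete experience in treating patients with diverse cultural backgrounds. One is described as follows: "The participants are further asked whether they are supervised in the field of transcultural therapy". The items come from a preliminary study, and their exact wording is not reproduced.

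On the training, the Didactics section says: "After each module, participants receive written feedback from a supervisor about the completed exercises and upcoming questions". Section {11c} adds: "Adherence is further supported by the feedback of a supervisor, who communicates with the participants at least once a week". Section {5d} describes the role in these words: "The supervisors are in charge of supervising the participants, i.e., they give feedback on the modules completed".

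On timing, section {13} says of the waitlist group: "After the 2-month follow-up assessment, they will start the training". Section {18a} says that primary and secondary outcomes "will be collected at each time point of measurement (pre, post, follow-up 1, follow-up 2"). Section {20a} compares the arms on the secondary outcomes over pre, post and follow-up 1 at p < .05. Section {17a} states that nobody is blinded, and all data are self-reported.

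**The concern.** The item is meant to record something about the participant's clinical practice. The intervention supplies contact that the protocol also calls supervision, on the same subject, and only one arm has it during the controlled comparison. A training-group member with no outside supervision could answer yes at post, while a waitlist member in the same practice situation would answer no. Neither has changed practice.

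Any error of this kind runs in one direction. If a group difference on this item were reported as more therapists taking up transcultural supervision for their clinical work, the claim could rest partly or wholly on allocation. An analysis cannot repair this afterwards, because a bare yes does not show which supervision was meant.

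**Working it through.** **Step 1: who can have a study supervisor at each assessment**

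| Assessment | Training group | Waitlist group |
|---|---|---|
| Pre (t0) | no | no |
| Post (t1) | yes, over the six weeks just ended | no |
| 2-month follow-up (follow-up 1; t2 in the waitlist group) | training ended about two months before | no |
| After the waitlist group's own training (from t3) | training ended earlier | yes |

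Baseline answers, and waitlist answers up to and including t2, mean the same whether or not the item excludes study contact, because no study supervisor exists yet. The ambiguity in the controlled comparison is confined to the training arm at post and follow-up 1.

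**Step 2: size of a possible artefact**

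The plan states no figure for this item, so there is nothing to reproduce. The inputs are:

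- n = 87 per arm, from N = 174 at 1:1 (sections {14} and {8}), with complete data assumed.
- b, the true share with outside supervision, equal in both arms. This is assumed: 15%, with a range of 5% to 30%.
- q, the share of otherwise unsupervised trainees who count the study supervisor. This is assumed: 2% to 25%.
- Two-sided pooled two-proportion z test at 1.96, no real effect.

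The observed yes rate is b in the waitlist arm and b + (1 − b)q in the training arm, so the false difference is (1 − b)q.

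For b = 0.15 and q = 0.10: 0.85 × 0.10 = 0.085, that is 23.5% against 15%.
For b = 0.15 and q = 0.25: 0.85 × 0.25 = 0.2125, that is about 36% against 15%.

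The chance of a significant result, by exact enumeration of the two binomial distributions, is:

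| q | b = 5% | b = 15% | b = 30% |
|---|---|---|---|
| 2% | 7% | 6% | 6% |
| 5% | 21% | 11% | 8% |
| 10% | 58% | 29% | 16% |
| 25% | 99% | 91% | 67% |

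The matching false differences at q = 10% are 9.5, 8.5 and 7.0 percentage points. At q = 25% they are 23.8, 21.3 and 17.5 points.

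This is a single-time-point test at post, not the piecewise mixed model of section {20a}. It shows the order of magnitude only. With an item that excludes study contact, q = 0 and the false difference is 0 by construction.

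**The case against.** The strongest answer is that the item itself is not on view. The article paraphrases it in one clause, and a journal article normally leaves item wording to the questionnaire. The training is in German, and the terms participants actually see for the feedback-giver and for being supervised are not given. The abstract calls the same contact weekly written feedback from a trained psychologist. This stands: the gap is shown for the protocol's description, not for the questionnaire.

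Second, the sentence in section {5d} limits the supervising to feedback on completed modules. The Didactics section describes written comments built from templates and individualised, with answers to questions. Nothing describes supervision of the participant's cases. Respondents are licensed psychologists or have at least a year of training, and many would not count module feedback. This also stands. It argues for a low q, but it does not make q zero.

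Third, the item is phrased in the present tense, so the artefact should be weaker at follow-up 1. That is accepted. The Limitations section does say that "the exchange with the accompanying supervisor remains possible at any time", but it says so when discussing the training format, and it does not establish supervision after the training has ended.

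Fourth, sections {6a} and {7} name the number of patients, satisfaction and experienced competence, and do not mention supervision. The protocol ties no hypothesis to this item.

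A reader might infer that the item simply measures receipt of the intervention, or that a false positive is likely. The documents support neither reading. They show that miscounting is possible and which way it would run, but not how often it would happen.

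**Conclusion.** The point holds in a limited form. As the protocol describes it, the item leaves room for training-arm participants to answer yes on account of the study's own supervisors, mainly at post, and any such error favours the training. It touches one of eight exploratory items.

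The size cannot be fixed from the documents. Under the stated assumptions the inflation runs from negligible (6% to 7% significant at q = 2%) to large (67% to 99% at q = 25%). The conclusion also depends on the questionnaire containing no exclusion already. It is a worthwhile, inexpensive clarification and no threat to the trial's main result.

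**What to change.** First check the questionnaire. If it already excludes study contact, say so in one line and nothing else is needed.

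If it does not, add to the item at every assessment after baseline: *for your own clinical work, not counting the feedback or supervisors of this study*. Baseline can stay as it is.

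Report training-arm post and follow-up 1 answers already collected under the current wording descriptively only. Do not interpret a group difference in them as uptake of clinical supervision.

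The work is one clause in an online survey and one sentence on the analysis. Recruitment began in April 2023, so some answers will probably already be in. The between-arm test of this item loses the affected training-arm answers at both time points, and the wording departs slightly from the preliminary study's item.

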#### Satisfaction with training

In order to be able to adapt and improve the training, the training will be assessed in terms of satisfaction and acceptance. The questions were designed specifically for the study and adapted to the training content. They were tested and validated for comprehensibility during piloting. The questions refer to 5 sections: scope and practicability (5 items, e.g., “I was able to complete the training within the six weeks without any timing issues.”), formal design (5 items, e.g., “The design of the training platform was engaging.”), content (24 items, e.g., “The modules were varied.”), relevance to practice (4 items, e.g., “The training has made me feel more competent working with patients with diverse cultural backgrounds.”), and personal experience (8 items, e.g., “My expectations of the training were met.”). These questions are assessed on a 6-point Likert scale, from 1, strongly disagree, to 6, strongly agree. Participants further have the opportunity to write down any other comments and suggestions for improving the training in a free text field.

#### Control variables

In the pre-training assessment, sociodemographic data are collected through 18 items. In addition to standard socio-demographic information (age, gender, nationality), participants are asked whether they would perceive themselves as having a migration background. They are further asked whether they speak more than two languages fluently and whether they do/did any volunteer work for refugees or migrants.

In addition, questions are asked about therapeutic practice: duration of psychotherapeutic activity, specialization (behavioral therapy, depth psychology, etc.), and workplace (own practice, clinic, research institution, etc.). Finally, participants are asked whether, and if so to what extent, training with a focus on “culture in psychotherapy” has ever been completed.

### Participant timeline {13}

Via a link, participants can access the detailed description and the inclusion criteria of the study online. After accepting the informed consent, the participants will be forwarded to the pre-training assessment (t0). During the pre-training assessment, the control variables as well as the primary (Multicultural Counseling Inventory and OnTracc) and secondary outcomes are measured. The participants will subsequently be randomized. The TG will directly start with the training. After the training (t1) and 2 (t4) and 6 months later (t5), the assessments are carried out again. The WG will complete a control assessment (t1) after the training group has completed the training. They will also complete the 2-month follow-up assessment (t2). After the 2-month follow-up assessment, they will start the training. After the training (t3) and 2 (t4) and 6 months (t5) later, they will complete the assessments. For the participant timeline, please refer to Fig. 1.

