##### Format

The online training lasts 6 weeks. Every week a new module is unlocked, which is expected to take between 1 and 2 h for the participants to complete. Each module contains between 9 and 10 web pages. Modules can be interrupted at any time and continued later, but it is helpful to divide a module into no more than two blocks per week. It has proven helpful to allow 2–3 days between the completion of one module and the processing of the following module. Research indicates that spacing learning units enhances retention [46]. The training includes a symbol that appears twice per module to remind participants to take a short break.

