### Plans to promote participant retention and complete follow-up {18b}

Participant retention is promoted through weekly contact with a supervisor. For the follow-up surveys, participants are contacted by email. If the questionnaires are not completed within seven days, a reminder email will follow. If the questionnaire is still not answered, another e-mail will follow within a week. After 4 weeks, a last reminder to fill in the questionnaire follows. The emails emphasize the importance of completion in order to improve training and, in the long term, the availability of qualified training. At the same time, reference is made to the continuing education credit that participants receive after completing the final questionnaires. As all questionnaires can be answered online, participants can fill in the questionnaires flexibly and from any place. No further promotional measures will be taken to increase participation.

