## Trial status

The trial was registered on February 21, 2023, under https://www.bfarm.de/DE/Das-BfArM/Aufgaben/Deutsches-Register-Klinischer-Studien/_node.html, identifier DRKS00031105. Recruitment has started in April 2023 and is expected to be completed in April 2024. The protocol presented is the first version (July 04, 2023).

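### Post and 2-month assessments follow the trainee's own finish in one arm and a group event in the other, so the arms can be compared at unequal times since randomisation and stalled trainees can go unassessed

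*Protocol article*

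**What the plan says.** All places are in the protocol article.

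- **Training group, Participant timeline {13}:** trainees start directly after randomisation. "After the training (t1) and 2 (t4) and 6 months later (t5), the assessments are carried out again".
- **Waitlist, same section:** "The WG will complete a control assessment (t1) after the training group has completed the training". A 2-month follow-up comes next, and then the waitlist's own training. The abstract uses the same anchor: the waiting period ends 2 months after the training group's training ends.
- **Pacing:** under Format, training lasts 6 weeks and "Every week a new module is unlocked". Under Didactics, "Through sending the feedback, the next module will be unlocked".
- **Inactivity, Strategies to improve adherence {11c}:** reminders go out after 5 days and again a week later. "If neither the training is worked on nor are the emails answered for 3 weeks", a last e-mail is sent. After 7 more days without work or a reply, participation is deleted and the person counts as having dropped out of the study.
- **Entry, Trial status:** "Recruitment has started in April 2023 and is expected to be completed in April 2024".
- **Analysis:** Statistical methods {20a} specifies intention-to-treat piecewise linear mixed models over pre, post and follow-up 1. Section {20c} says that everyone randomised enters the analysis.

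The text gives no time since randomisation for t1 or follow-up 1 in either arm.

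**The concern.** The primary contrast compares arms at time points treated as common to both. As written, the trainee's clock depends on how fast that person works and how fast feedback is returned. The waitlist participant's clock depends on an event that belongs to other people. Two things are at stake.

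1. **Elapsed time.** If a trainee's interval stretches and the waitlist's does not, change from retesting, caseload or outside events enters the group contrast. In a piecewise linear model the slope also depends on the interval assumed for each segment.
2. **Who is measured.** The route to t1 passes through completing the training in one arm only. If trainees who stall supply no post data while all waitlist participants are invited, the observed trainees are the more engaged ones. A mixed model can keep the others through their baseline, but it must then assume that their missing scores are predictable from observed data. Outcomes are unblinded self-report, so selection of this kind would probably flatter the training.

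**Working it through.** **Inputs.** Six modules, nominally one per week (Format); follow-up 1 is 2 months after t1 (Participant timeline {13}). Two months = 2 × 365.25 / 12 / 7 = 8.7 weeks. Paces other than one week per module are assumptions.

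**Step 1: the plan's own schedule.** t1 = 6 × 1 = week 6; follow-up 1 = 6 + 8.7 = week 14.7. If the waitlist is sent t1 at the nominal six weeks, its times are the same. On paper the arms match.

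**Step 2: slower paces that the rules do not exclude.** With w weeks per module, t1 = 6w and follow-up 1 = 6w + 8.7.

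| Weeks per module (assumed) | Trainee t1 | Trainee follow-up 1 | Later than nominal waitlist |
|---|---|---|---|
| 1 | 6 | 14.7 | 0 |
| 2 | 12 | 20.7 | 6 |
| 3 | 18 | 26.7 | 12 |

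At 2 weeks per module, the pre-to-post interval is 12 / 6 = 2 times as long as that of a waitlist participant assessed at week 6.

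**Step 3: the waitlist trigger.** Trainees start directly after randomisation and recruitment runs from April 2023 to April 2024. They therefore finish on dates spread over about a year, and no one date marks completion by the training group. The study team has to supply a rule that the text does not give.

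**Step 4: who falls due for t1.**

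- A trainee who keeps working, however slowly, reaches t1 late.
- A trainee who stalls but answers e-mails does not meet the deletion rule, which needs both no work and no reply. No date for t1 is stated.
- A trainee who stalls silently is deleted and counted as out of the study.
- A waitlist participant faces no activity requirement before t1 or the 2-month assessment.

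Section {20b} also plans to relate completed modules to outcomes. That needs outcome data from people who did not complete.

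**Step 5: is this a power problem?** The planned N can be reproduced under one assumption. One-sided, n per arm = 2(1.645 + 1.645)² / 0.5² = 86.6, so 87 per arm and N = 174. Two-sided, 2(1.960 + 1.645)² / 0.5² gives 104 per arm and N = 208. The article states neither sidedness nor a pre-post correlation, so this match does not identify the method used, and nothing here depends on it. Suppose t1 is lost in the training group only:

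| Assumed loss | Power, one-sided | Power, two-sided |
|---|---|---|
| 0% | 0.951 | 0.910 |
| 10% | 0.941 | 0.894 |
| 20% | 0.928 | 0.875 |
| 30% | 0.911 | 0.849 |

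These losses are modest. The issue is bias from selective missingness and unequal timing, and the article gives no figure from which to size that bias.

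**The case against.** The strongest reply is that six weeks is the design throughout. Eligibility asks for time to work 1–2 hours per week for 6 weeks, reminders start after 5 days, and the nominal times coincide. Assessing at the end of training is a common choice. Nothing says that the questionnaire is withheld from non-completers, and the retention section {18b} describes e-mailed questionnaires and reminders without a completion condition. Fig. 1 is not shown here and may give weeks. Recruitment had begun before this protocol version, so a new anchor would mix two schedules.

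Much of this stands, and it limits the point. A reader might infer several stronger things that the documents do not support:

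- **That the arms are in fact compared at different times.** The rules allow it; the article does not state it.
- **That training will run to 24 weeks.** Silence for 3 weeks plus 7 days at each of six modules gives 6 × 4 = 24 weeks. This needs a restart just before deletion every time, and nothing suggests how often that would happen.
- **That early waitlist participants wait over a year for t1.** This follows only if the whole arm must finish first. The Limitations section says that waitlist participants should not wait too long, which points to a wait per participant.
- **That slow trainees never reach t1.** Only those who stall lack a date.
- **That weekly unlocking and unlocking by feedback conflict.** Feedback is weekly, so the two are compatible.
- **That labels t4 (training group) and t2 (waitlist) for the 2-month follow-up will corrupt the analysis.** The model uses pre, post and follow-up 1, so this is clerical.
- **That late questionnaire replies add imbalance.** "After 4 weeks, a last reminder to fill in the questionnaire follows" applies to both arms.

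The reply does not remove the written triggers. If Fig. 1 gives weeks, the text must be reconciled with it. Section {31c} says that this article is the complete protocol, so the point cannot be assumed settled elsewhere.

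**Conclusion.** The point holds in a limited form. Followed as written, the rules can make elapsed time and missing post data depend on adherence in the training group only, while the analysis assumes common time points and promises intention-to-treat.

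The size depends on pace. There is no gap at one week per module and six weeks at an assumed two, taking waitlist t1 at the nominal week 6. How many trainees will run late or stall is unknown, and so is any drift in waitlist scores over the extra weeks, so the bias cannot be sized from the document. The planned N of 174 is unaffected. This should be changed because the remedy is specific and cheap; it is not shown to invalidate the trial.

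**What to change.** 1. **Participant timeline {13}:** send t1 and the 2-month assessment at the same fixed times since randomisation in both arms. For example, use the nominal 6 weeks, or 6 weeks plus a short slack, and then 2 months later. Apply one response window, and send both to every randomised participant whatever the number of modules completed.
2. **Strategies to improve adherence {11c}:** treat a stalled trainee as having stopped the training, not the study, unless that person withdraws from assessments.
3. **Data and analysis:** record actual training completion and assessment dates. For participants already enrolled under the present triggers, use the actual assessment dates in the model.
4. **Tidying:** give the 2-month assessment the same label in both arms, and check the text against Fig. 1.

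**Cost.** Revised wording, a changed e-mail schedule, and the ethics approval, protocol update and registry change foreseen in section {25}. Any slack also lengthens the waiting period slightly. Some trainees will be assessed before finishing, which may slightly reduce the post effect, but that is the effect an intention-to-treat comparison is meant to estimate.
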